## Abstract

**Introduction:**

Patients diagnosed with coronary artery disease (CAD) are currently treated with medications and lifestyle advice to reduce the likelihood of disease progression and risk of future major adverse cardiovascular events (MACE). Where obstructive disease is diagnosed, revascularisation may be considered to treat refractory symptoms. However, many patients with coexistent cardiovascular risk factors, particularly those with metabolic syndrome (MetS), remain at heightened risk of future MACE despite current management.

Cardiac rehabilitation is offered to patients post-revascularisation, however, there is no definitive evidence demonstrating its benefit in a primary prevention setting. We propose that an intensive lifestyle intervention (Super Rehab, SR) incorporating high-intensity exercise, diet and behavioural change techniques may improve symptoms, outcomes, and enable CAD regression.

This study aims to examine the feasibility of delivering a multicentre randomised controlled trial (RCT) testing SR for patients with CAD, in a primary prevention setting.

**Methods and analysis:**

This is a multicentre randomised controlled feasibility study of SR versus usual care in patients with CAD. The study aims to recruit 50 participants aged 18–75 across two centres. Feasibility will be assessed against rates of recruitment, retention and, in the intervention arm, attendance and adherence to SR. Qualitative interviews will explore trial experiences of study participants and practitioners. Variance of change in CAD across both arms of the study (assessed with serial CT coronary angiography) will inform the design and power of a future, multi-centre RCT.

**Ethics and dissemination:**

Ethics approval was granted by South West—Frenchay Research Ethics Committee (reference: 21/SW/0153, 18 January 2022). Study findings will be disseminated via presentations to relevant stakeholders, national and international conferences and open-access peer-reviewed research publications.

**Trial registration number:**

ISRCTN14603929.

Strengths and limitations of this studyThis is a multicentre randomised controlled feasibility study.This study will use a mixed-methods approach, collecting quantitative and qualitative data, assessing a novel rehab programme (Super Rehab).This study is not designed to determine efficacy or cost-effectiveness and is limited to informing the feasibility of a larger trial of Super Rehab.Contemporary CT measurements of coronary artery inflammation and plaque will be acquired.If it is determined that a larger, multi-centre trial is feasible, this study will provide key data to improve its design.

## Introduction

Coronary artery disease (CAD) remains the most common cause of premature death in the UK and its treatment consumes substantial healthcare resources. Overall plaque burden has recently been shown to be a more sensitive marker for risk of future adverse cardiovascular event than luminal stenosis, which has historically been the focus in CAD treatment.^1^ Plaque regression, not just stabilisation, is a novel end-point in the treatment of CAD and has been used in pharmaceutical trials.^2 3^ Disease regression is the target in several other disease modalities where previously it was not thought possible, for example, type II diabetes.^4^

The role of poor diet and physical inactivity is well recognised in the pathogenesis of CAD.^5^ Lifestyle intervention studies focusing on physical activity and diet improve cardiovascular fitness (which reduces cardiovascular risk), metabolic parameters, and psychological and self-perceived health.^6–8^ Exercise training increases angina-free activity threshold, attenuates disease progression and improves event-free survival.^9^ Lifestyle intervention reduces systemic inflammation.^10^

A limited number of small studies combining a lifestyle intervention with routine care have shown the potential for CAD regression,^11–13^ indicating both a preventative and therapeutic impact.^14^ Plaque regression has been observed at 12 months and complete plaque regression has been demonstrated in case reports of patients with significant disease without coronary intervention (eg, stents).^15^ However, the current evidence-base is of insufficient quality to justify a shift to healthcare delivered preventative programmes in a chronic coronary syndrome (CCS) population (ie, established, stable CAD). Such a shift in practice requires evidence from rigorous, adequately powered, randomised controlled trials (RCT) with suitable endpoints to persuade both commissioners and healthcare professionals that this clinical pathway is cost-effective.

A healthcare delivered lifestyle intervention, cardiac rehabilitation (CR), exists for patients further down the CAD pathway who have suffered an MI or required coronary revascularisation with stents or bypass surgery. A Cochrane Review reported that while exercise-based CR appears to improve cardiovascular mortality, further research is required in higher risk CCS groups in a primary prevention setting.^9 16^ This is despite >50% of MI resulting from non-obstructive plaque, highlighting the importance of robust treatments for this patient population.^17^

Super Rehab (SR) has been designed to reflect the evolution in lifestyle intervention practices since the advent of traditional CR, incorporating the balance of recent evidence, the likelihood of patient adherence and cost benefits. Specifically SR is a cardiology-led intervention incorporating high-intensity interval training (HIIT), updated best-practice dietary advice and current behavioural change techniques.

### Exercise

HIIT, which comprises alternating periods of high intensity aerobic exercise with light intensity recovery periods, has additional benefits over conventional moderate-intensity exercise incorporated into CR.^18–20^ Aerobic capacity (VO_2_ max), is an independent predictor of all-cause mortality and cardiovascular prognosis.^6^ HIIT achieves a greater improvement in VO_2_ max, improves outcomes in CAD patients^18^ and is supported by robust safety data.^21^ SR incorporates a modified version of the Norwegian 4×4 min HIIT model, which has been received well by CAD patients.^22^

### Diet

SR integrates best-practice dietary advice for atherosclerotic cardiovascular disease and CAD patients, which has evolved to incorporate reduced refined carbohydrate and sugar content, and healthier fats and proteins. Evidence has demonstrated additional improvements in cardiovascular risk, atherosclerotic burden, systemic inflammation, glucose and blood pressure control.^23–26^

### Delivery

Traditional CR pathways have well-documented low attendance rates, consistently <50%.^27^ To improve compliance and adherence, SR adopts evidence-based strategic behavioural intervention techniques to enhance the potential for patients to adopt and sustain changes promoted during SR.^28 29^ This includes techniques that promote motivation, self-regulation and support^30^ and an autonomy supportive (patient-centred) delivery style.^31^

CT coronary angiography (CTCA) is now the mainstay investigation in new onset stable chest pain of suspected cardiac origin. CTCA provides an excellent, non-invasive tool for tracking change in coronary plaque,^32 33^ while radiation doses are low and reducing.^34^ Imaging techniques now enable the assessment of additional measures that are highly predictive of future risk. This includes: (1) *pericoronary fat attenuation index* (FAI)—a sensitive CT-derived biomarker of coronary inflammation that out-performs all other cardiovascular disease risk-stratifications^35 36^; (2) *high-risk plaque features*—morphological markers of vulnerability based on the composition and location, which predict MI risk^37^ and (3) *fractional flow reserve* (*FFR_CT_*)—a computational fluid dynamics algorithm that non-invasively estimates flow change across a plaque to determine likelihood of obstructive disease, with adverse haemodynamics denoting risk of future MI.^38^

We hypothesise that SR will improve symptoms and cause CAD regression, reducing the risk of MI and death. To change current clinical practice and integrate SR into standard care, a suitably powered RCT is required to establish efficacy using CAD-specific prognostic clinical outcomes, tracked via changes on CTCA. The present study aims to examine the feasibility of delivering a subsequent multi-centre RCT.

## Methods and analysis

### Study design

A multicentre two parallel-arm feasibility study randomising 50 patients (1:1) to Usual Care or SR plus Usual Care to establish the feasibility of conducting a subsequent, larger and powered multicentre RCT. Figure 1 provides a study flow-chart and the protocol follows the Standard Protocol Items: Recommendations for Interventional Trials reporting guidelines.^39^

**Figure 1 F1:**
[figure not shown]
Study flow-chart.

### Study aim

To establish the feasibility of delivering and evaluating a definitive RCT of SR with Usual Care vs Usual Care only in the target population.

### Study objectives

As a feasibility study, the primary objective is to assess the feasibility of delivering the proposed study design testing the efficacy of SR. Feasibility criteria assessed include:

Recruitment rates: the proportion of eligible patients who accept the invitation to participate.Retention and adherence: the proportion of participants who complete the study and, for those in the intervention group, the proportion of offered sessions completed.Acceptability of the intervention, study design and outcome measures as well as participants’ and practitioners’ experiences of SR.

Additional secondary objectives include:

Evaluate and refine data-collection procedures and outcomes measures.Pilot the use of routine clinical data (body mass index (BMI) and HbA1c) in identifying CAD patients with MetS.Obtain preliminary data for CAD regression to inform power calculations for a subsequent RCT.

### Study population and setting

Participants will be prospectively identified via routine clinically indicated CTCA lists at Royal United Hospitals Bath NHS Foundation Trust and North Bristol Trust. In line with the National Institute for Health and Care Excellence (NICE) guidelines on the assessment of patients with stable chest pain,^40^ patients with new-onset chest pain and no prior history of CAD are referred for a CTCA to assess for the presence and severity of CAD. This scan will be incorporated into screening and outcome assessments.

Patients with CAD who also have metabolic syndrome (MetS) are a particularly high-risk CAD group, representing up to half of all CAD patients^41^ and have a threefold increased risk of death.^42 43^ MetS is a cluster of conditions including abdominal obesity, raised triglycerides, high-density lipoprotein (HDL-cholesterol) or fasting glucose and hypertension.^44^ MetS not only increases the risk of CAD, but predicts more severe CAD and worse prognosis.^45 46^ Inflammation is a potent driver of atherosclerosis,^47^ risk of myocardial infarction (MI)^48 49^ as well as disease progression in MetS.^50^ Thus, CAD-MetS patients with evidence of inflammation are an important cohort with notable residual risk despite current treatments. A targeted rehabilitation programme may offer a significant benefit to this sizeable patient group.

### Inclusion criteria

Aged 18–75 years at consent.CTCA demonstrates CAD with plaque causing a stenosis of ≥25% in ≥1 coronary artery.Evidence of coronary inflammation (FAI>−70.1 HU or FAI-score (relative to age-matched and sex-matched patients) ≥75th percentile in the left anterior descending or right coronary artery or ≥90th in the circumflex^35^).MetS, defined as ≥3 of the following within 6 months of CTCA^44^High abdominal waist circumference (≥94 cm males, ≥80 cm females).Hypertension (≥130/85 mm Hg or on treatment).Diabetes mellitus or raised fasting glucose or HbA1c (glucose≥5.6 mmol/L, HbA1c≥42 mmol/L).Reduced high-density lipoprotein (≤1 mmol/L males, <1.3 mmol/L females).Raised triglycerides (>1.7 mmol/L).

### Exclusion criteria

Participants will not be eligible if they have conditions that preclude high-intensity exercise, including:

CAD requiring revascularisation.Unstable angina.New York Heart Association class III/IV heart failure or severe left ventricular impairment.Severe valve disease.Significant cardiomyopathy (as assessed by a cardiologist).Severe hypertension (defined as blood pressure>180/120 mm Hg).Uncontrolled cardiac arrhythmia.Prior aortic dissection.Recent acute pulmonary embolus, deep vein thrombosis, stroke or transient ischaemic attack.Severe autonomic or peripheral neuropathy.Acute systemic illness or fever.Significant acute or chronic renal failure.Pulmonary fibrosis or interstitial lung disease.Physically unable to participate in exercise.Clinically significant ECG abnormality at the screening visit, which, in the opinion of a Cardiologist, exposes the subject to risk by enrolling in the trial.

Additionally, patients with a history of prior MI or coronary revascularisation, severe coronary calcification that precludes assessment of the coronary lumen on CTCA, current participation in another intervention-based study, and pregnant or breastfeeding individuals will be excluded.

### Amendments to eligibility criteria

During the initial recruitment period, it became clear that the original eligibility criteria (high BMI (>28 kg/m^2^) and abnormal glucose control (HbA1c>42 mmol/mol or >6%)) was incompletely capturing patients with MetS. Thus, a substantial amendment was submitted to the ethics committee to allow recruitment of participants who met the international consensus criteria for MetS (outlined in the inclusion criteria above).^44^ The FAI criterion was also adjusted to ensure younger patients with high inflammation relative to age-matched and sex-matched controls (FAI-score) were captured, as well as patients recruited based on their absolute FAI value (approved 9 May 2022).

A further substantial amendment was submitted to the ethics committee to ensure participants with a raised HbA1c could participate, as fasting glucose levels were incompletely capturing patients with poor longer term glucose control (approved 12 July 2022). A non-substantial amendment clarified that participants needed to have met eligibility criteria within 6 months of their CTCA (approved 20 September 2022).

### Sample size

As a feasibility study, there is no primary outcome measure to inform a power calculation. However, a sample size of 25 in each arm is sufficient to estimate feasibility outcome proportions for acceptability rates of 64% (with 90% CI 46% to 80%) and adherence rates of 84% (90% CI 67 to 93%). The corresponding intervals for recruitment rate will be more precise as the number of potential participants will be>50.

### Screening and consent

Initial prescreening identifies potential participants who meet CAD inclusion criteria on their clinically indicated CTCA. Potential participants will be informed of the experimental protocol in writing and invited for a clinic assessment where they will complete screening with a clinician. Eligible and willing participants will be asked for written informed consent obtained according to Good Clinical Practice guidelines, and Usual Care will be instituted.

### Randomisation

Following completion of all baseline assessments, participants will be block randomised (1:1) to SR and Usual Care or Usual Care only. Randomisation will be performed using a web-based platform (Sealed Envelope: https://www.sealedenvelope.com/) in permuted blocks of four with stratification by sex using an allocation sequence generated at random.

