#### Blinding

The nature of the intervention (SR) prevents blinding of the participants and clinicians to their trial arm. However, statistical, health economic and clinical outcome analyses (including CTCA (FAI, FFR_CT_, stenosis) and blood results) will be completed blinded to study allocation.

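### A single fixed block size of four, stratified by sex only, in an open trial lets anyone who sees both centres' allocations know up to one third of them in advance

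*Protocol article*

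**What the plan says.** The Randomisation section of the protocol article states that "participants will be block randomised (1:1) to SR and Usual Care or Usual Care only", and specifies "permuted blocks of four with stratification by sex". Four is the only block size given. Sex is the only stratification factor. Centre is not one, although there are two centres, so each of the two sex lists runs across both.

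The same section sets the timing ("Following completion of all baseline assessments") and the mechanism ("Randomisation will be performed using a web-based platform").

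The Blinding section says: "The nature of the intervention (SR) prevents blinding of the participants and clinicians to their trial arm". Statistical, health economic and clinical outcome analyses are to be done blind, with CT coronary angiography (CTCA) and blood results named. The cardiopulmonary exercise test (CPET) is not named there.

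Under Study governance, the trial management group contains the whole research team and oversees daily running. The article does not say who sees past allocations across centres, or whether recruiting staff knew the block size while recruiting.

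**The concern.** A web platform hides the allocation list. It does not hide an allocation that can be deduced. With a fixed block of four at 1:1, each block holds two allocations to each arm. Once two have gone to one arm, the rest of the block is determined. In an open trial, past allocations are visible to whoever follows the participants.

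The steps that call for judgement all come before randomisation:

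- Some exclusions rest on opinion, such as the cardiologist's view of a cardiomyopathy or ECG finding, or physical inability to exercise.
- Consent follows a clinic assessment with a clinician.
- The CPET runs to volitional exhaustion, and a participant with worrying discomfort leaves the study at that point.

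Randomising after baseline therefore does not by itself protect against someone who already knows the next slot at consent or at the test.

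What is exposed is who enters each arm. That bears on two things this study is meant to deliver. One is SR adherence, which is measured in one arm only and is a progression criterion. The other is the by-arm change data intended to guide the sample size of the later trial.

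**Working it through.** The article gives no predictability figure to reproduce, so the check starts from the design.

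**Inputs from the protocol article.** Block size 4, ratio 1:1 and two sex lists (Randomisation); 50 participants and two centres (Abstract, Study design). **Assumptions.** The split of recruitment between centres and between sexes is not stated, so ranges are used.

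**1. Observer who sees the whole sex list and knows the block size.** There are six possible blocks (arrangements of AABB). An allocation is certain when one arm is already used up.

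| Position in block | Probability that it is certain | Best guess correct |
|---|---|---|
| 1 | 0 | 1/2 |
| 2 | 0 | 2/3 |
| 3 | 1/3 (first two match) | 2/3 |
| 4 | 1 | 1 |

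- Certain: (0 + 0 + 1/3 + 1)/4 = 1/3 = 33.3%.
- Best guess: (1/2 + 2/3 + 2/3 + 1)/4 = 17/24 = 70.8%.

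With 50 participants, two lists and incomplete last blocks, simulation (4,000 runs per setting) gives about 31.7% certain for expected sex splits of 50:50, 70:30 and 80:20. That is 0.317 × 50 ≈ 16 allocations.

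**2. Observer who sees only one centre's arms but knows the block position.** Certainty now requires that both allocations to the used-up arm were made at the observer's own centre. Let p be the share recruited at one centre. The chance that those two and the current participant are all at the same centre is p³ + (1 − p)³. The certain share is therefore (1/3) × [p³ + (1 − p)³] for complete blocks, or 0.317 × [p³ + (1 − p)³] allowing for incomplete ones.

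| Centre split (assumed) | p³ + (1 − p)³ | Complete blocks | Allowing for incomplete blocks |
|---|---|---|---|
| 50:50 | 0.250 | 8.3% | 7.9% |
| 70:30 | 0.370 | 12.3% | 11.7% |
| 90:10 | 0.730 | 24.3% | 23.1% |

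Direct simulation gives the same values (7.9%, about 11.7% and 23.2%). An observer without the other centre's counts cannot tell where a block begins, and certainty is then close to nil.

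**3. Randomly varying block sizes.** Here an observer sees everything and knows the possible sizes but not the order. The block state was tracked by Bayes' rule (1,500 simulated trials of 50).

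| Block sizes | Certain | Best guess correct | Largest end-of-list imbalance |
|---|---|---|---|
| 4 only | 31.4% | 70.2% | 2 |
| 4 and 6 | 5.8% | 68.5% | 3 |
| 4, 6 and 8 | 2.3% | 67.3% | 4 |

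Out of 50 participants, certain allocations fall from about 16 to about 3 (0.058 × 50 = 2.9) or about 1 (0.023 × 50 = 1.2).

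**4. How sensitive the adherence criterion is.** Success criteria requires the lower 90% exact limit to reach 70%. With 25 SR participants, 21 adherent gives a lower limit of 67.0% (not met) and 22 gives 71.8% (met). One participant can change the classification. This shows that the composition of the SR arm matters. It does not estimate any bias.

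**The case against.** A reader might infer that recruiting staff in general know one third of allocations with certainty. The documents do not support that. They say clinicians cannot be blinded to trial arm, not that staff at one centre see the other centre's allocations. Because the lists are not split by centre, single-centre staff lack much of the information needed. The make-up of the trial management group makes a cross-centre view possible, but does not show that allocation logs were shared. Nor does a block size printed in a journal article show that recruiters knew it while recruitment was open. This objection stands, and it makes one third an upper bound.

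Timing also weakens the risk. The figure applies at the moment of randomisation, whereas steering would have to occur earlier. The baseline period includes seven-day recordings, and foreknowledge lapses if another participant of the same sex is randomised in the meantime. This stands too. It reduces the risk without removing it.

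A reader might also infer that the recruitment criterion and the CTCA measurements are compromised. The recruitment rate is a single proportion, not split by arm, and retiming an enrolment does not alter it. The first CTCA is a routine clinical scan that precedes recruitment, and CTCA analysis is blinded, so only patient selection could affect those data. For the CPET, attainment criteria and a repeat-test rule limit coaching, and the test is not a progression criterion.

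Finally, varying the block size barely lowers best-guess accuracy. That is correct. The gain is in removing certain knowledge.

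What survives is narrower: blinded reading protects measurement but not who enters each arm, and a single block size makes prediction easier than it need be.

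**Conclusion.** The point holds in limited form. A single block size of four in an open trial allows certain foreknowledge of at most one third of allocations (about 31.7% with 50 participants). This applies to someone who knows the block size and sees every earlier allocation in the sex list at both centres. For staff who see one centre only and know the block position, the share is about 8% to 23%, depending on an assumed centre split of 50:50 to 90:10. Without the block position it is close to nil.

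The exposed items are the composition of the arms, and through it SR adherence and the by-arm change data, together with the baseline CPET. Neither the direction nor the size of any effect can be derived from the documents, and nothing in them shows that steering occurred. The study is not designed to test efficacy and already uses web-based allocation after baseline, so the weakness is minor here. It would matter more if the scheme were carried into the definitive trial.

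**What to change.** Replace the single block size with randomly varying sizes, for example 4 and 6, or 4, 6 and 8. Have them set by someone outside the recruiting team and withheld from recruiting staff until recruitment ends.

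The cost is a configuration change in the randomisation service. The largest possible imbalance at the end of each sex list rises from 2 to 3 (sizes 4 and 6) or 4 (sizes 4, 6 and 8).

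If recruitment is already complete, report who could see allocations at both centres and who knew the block size, and adopt varying blocks in the definitive trial.
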